## Abstract

**Introduction:**

South Asia carries the burden of a rapidly changing climate with floods and extreme heat. These disasters further translate into mental health distress, financial stress and detrimental effects on well-being, with women being the most vulnerable. This study aims to demonstrate that mental health screening, referral and resilience-building group sessions can be successfully administered by community health workers and primary health facility staff in a flood-affected rural population of women in Pakistan and provide evidence on the effectiveness of this approach for improving their mental health status.

**Methods and analysis:**

A quasi-experimental design with a comparison group will be used for the study, preceded by a formative phase. The formative phase evaluated the feasibility of mental health screening by Lady Health Workers (LHWs) in flood-affected areas using a qualitative approach such as focus group discussions and in-depth interviews. Manuals developed by the study team of mPareshan will be used to train LHWs, Lady Health Supervisors (LHS) and health facility staff. Following this, LHWs will briefly screen women aged 18 to 49 years, administer awareness-raising and resilience-building sessions and refer women who screen positive for depression or anxiety to a primary health facility. Physicians at the health facility will confirm the diagnosis and provide counselling to mild-moderate cases, while severe cases would be referred to specialists. Statistical evaluation of quantitative data and thematic content analysis of qualitative data will be conducted to assess the feasibility and impact of the intervention. This trial is registered at clinicaltrials.gov with number NCT06756165.

**Ethics and dissemination:**

The study acquired ethical approval from the Ethical Review Committee at Aga Khan University (2024-10475-30776) and the National Bioethics Committee (4-87/NBC-1158/23/481) in Islamabad. Approval was obtained from relevant provincial authorities. The trial will adhere to the ethical principles of autonomy, anonymity, confidentiality, equity and respect. All eligible participants will be provided with informed consent, details regarding the purpose and procedure of the study, and the right to withdraw at any time. Data and information will be anonymised and stored securely. Dissemination of the results of the trial will occur after its completion to stakeholders, participants and the public.

**Trial registration number:**

NCT06756165.

STRENGTHS AND LIMITATIONS OF THIS STUDYThere is an existing gap, and interventions have not been evaluated to cater to the mental health needs of women through a primary health system in a developing country context.The design of the trial is unique and has not been previously evaluated in a flood-affected rural setting.The methodology allows for evaluating the feasibility and cost-effectiveness of providing mental health awareness and resilience-building services in a community setting.The trial focuses on training community health workers for easier social integration with women in the setting.Results of the trial once published can inform policy in low and middle-income country contexts.

## Background

 Climate change has emerged as an alarming crisis in recent years with natural disasters escalating across the globe.^1^ Large-scale flooding, cyclones and heatwaves are just a few of the climate change-related disasters that threaten health infrastructure, resources for survival and shelter. The scarcity of basic needs increases physiological and mental health issues within disaster and flood-affected areas.^2^,^6^ According to WHO, an estimated 250 000 additional deaths related to climate change-induced malnutrition, diarrhoea, malaria and heat stress are predicted to occur per year between 2030 and 2050.^1^ Similarly, 150 000 lives have been lost every year for the past 30 years because of the detrimental effects of climate change.^6^ In addition to increasing mortality, disasters cause mental health distress, financial stress and other detrimental effects on well-being.^2^

South Asia carries a high burden of the rapidly changing climate, especially involving floods and extreme heat, with approximately 750 million people, half of the population across eight countries, experiencing at least one climate-related disaster in the past two decades.^4 7^ These communities have struggled due to the devastation of their physical and economic assets accompanied by psychological distress. Recurrent flooding and a lack of well-developed mental health services have worsened the living conditions of South Asians.^8 9^ In June 2022, Pakistan experienced extreme flooding causing immense destruction of crops, houses and health infrastructure,^10 11^ with a lack of clean drinking water, no access to basic services and the displacement of over 15 million people.^10^ Accompanied by political instability and stigma towards mental health, and absence of the integration of mental health services in primary healthcare, more than 13 000 individuals in Pakistan have been severely mentally and physically affected as a consequence of these floods.^9 11^

Moreover, vulnerable populations such as women, children and economically disadvantaged individuals are at a higher risk of adverse outcomes due to climate change-related disasters.^2 3^ It is essential that those disproportionately affected by these disasters are urgently catered to. In the rural areas of Sindh province, women and children experience higher rates of common mental health disorders (CMDs), gender-based violence and stress.^10 12^ The fear of potential calamities within individuals may serve as a predisposition to mental health conditions such as post-traumatic stress disorder 0r recurrent anxiety attacks.^11^ Screening and management of CMDs has still not been included in the primary healthcare programmes currently available to most women and children in rural Pakistan. Approximately 56% of Sindh lacks the availability of psychiatrists, sufficient mental health facilities and funding, and effective legislation.^10 13^ While the Sindh government has developed a limited curriculum to train Lady Health Workers (LHWs) about CMDs, it does not include community-based climate change and mental health resilience-building activities. Therefore, it becomes necessary to combat women’s psychosocial problems by incorporating sessions focused on community-based climate change and mental health resilience-building.

The traumatic impact of unforeseen displacement, loss of loved ones, destruction of agricultural livelihoods and absence of basic health services could be addressed, at least in part, through a feasible and effective community-based mental health programme. Moreover, community approaches to building climate resilience are part of Pakistan’s national climate change policy,^14^ further underscored by the recent massive floods. By catering to the mental health and flood-related issues of women in rural areas of Sindh through an existing primary health system, there may be hope for timely identification and delivery of appropriate intervention. This study aims to demonstrate that mental health screening, referral services and resilience-building group sessions can be successfully administered by community health workers and the primary health system within a flood-affected rural area of Pakistan and assess its effectiveness.

## Conceptual framework

The conceptual framework followed for the study was Bronfenbrenner’s ecological systems theory.^15^ It highlights the multifaceted levels of the healthcare system in relation to providing care to community members through effective delivery strategies, as depicted in figure 1. The microsystem works at an individual level involving issues regarding mental health, resilience and coping, and socioeconomic factors. The mesosystem further incorporates the lack of mental health services and gender-related disparities faced by the women of the community. At the community level, the exosystem focuses on providing services to the members through the LHW programme and the health department of Sindh. This level is essential to the research as the intervention focuses on evaluating the feasibility of integrating mental health services in LHW programme and government health facilities. The macrosystem working on a societal level provides clarity on the lack of governmental funds and effective policies by Pakistan Disaster Management Authority (PDMA), and the nuanced religious and societal barriers faced by women living in such communities which deter them from receiving and accessing quality healthcare. The chronosystem becomes significant as the natural disasters occurring in the region have worsened with time and combined with poverty and helplessness have led to the development of various mental health issues within our target population.

**Figure 1 F1:**
[figure not shown]
Conceptual framework based on the ecological systems theory by Bronfenbrenner. PDMA, Pakistan Disaster Management Authority; DDMA, District Disaster Management Authority.

## Methodology and analysis

### Objectives

The primary objective of the study is to assess the feasibility, acceptability and appropriateness of implementing a community-based mental health screening, referral and resilience-building intervention for adult women of reproductive age (WRA) in a flood-affected rural community of the district of Dadu in Sindh, Pakistan. The secondary objective is to assess the effectiveness of this community-based intervention.

### Study design

A quasi-experimental design with a comparison group will be used for the study. The preceding formative work investigated the knowledge, attitudes and practices regarding mental health issues and resilience-building in the population, and the likely acceptability, appropriateness and feasibility of the planned screening and referral intervention using focus group discussions (FGDs) and in-depth interviews (IDIs). Findings from the formative work were then incorporated into the development of the training materials for LHWs and health facility staff.

To evaluate the feasibility and effectiveness of the screening and referral intervention, LHWs will be trained to screen WRA through the brief two-item Generalized Anxiety Disorder scale (GAD-2)^16^ and brief two-item Patient Health Questionnaire (PHQ-2),^17^ and administer awareness-raising and resilience-building sessions along with appropriate referral to Basic Health Unit (BHU). Facility staff present within BHU will be trained to confirm the screening using the 7-item Generalized Anxiety Disorder scale (GAD-7)^18^ and the 9-item Patient Health Questionnaire (PHQ-9),^19^ provide counselling and refer severe cases to specialists at tertiary care facilities.

The study duration is January to December 2025 with the initial few months focusing on the formative phase followed by the actual intervention. This trial is registered at clinicaltrials.gov with number NCT06756165.

### Study site

This study will be conducted in the flood-affected areas of Dadu district in Sindh province, Pakistan. Dadu is located west of the Indus River, approximately 160 km north-northwest of Hyderabad. It was one of the worst-affected areas during the flooding in 2022, with an immense increase in water-borne illnesses and loss of shelter, basic resources and agricultural livelihoods.^20^

The district of Dadu is administratively subdivided into four Talukas: Dadu, Johi, Khairpur Nathan Shah and Mehar. The study will take place specifically in Taluka Khairpur Nathan Shah, where 8 flood-affected Union Councils (UCs) were purposely chosen as they were the most severely affected and assigned into two groups: 4 UCs for the intervention group (Gozo, Burira, Chor Qambar and Kande-Chukhi) located on the left side of the Taluka Headquarters and 4 UCs for the control group (Dhani Bux Bughio, Parya, Thalo and Sindhi Butera) located on the right side to maintain distance and avoid contamination. Each UC in both arms has one BHU and a 24/7 Maternal, Newborn and Child Health (MNCH) Center.

### Population

The target population for this survey will be WRA within the ages of 18 years to 49 years. This sample was selected due to its critical relevance to the study’s focus on mental health and the impact of climate-related disasters, particularly flooding, on vulnerable individuals. Women in this age range are often at heightened vulnerability, balancing the physical demands of reproductive health with the psychological stressors posed by displacement and environmental crises. Based on the formative work preceding this study, women experienced traumatic events including sexual violence, rape, as well as a lack of privacy and security. Maternal health was severely affected as many pregnant women faced severe complications, infections and death.

### Sample Size

The sample size was calculated based on an estimated anxiety prevalence of 25.6%. To detect a 20% relative difference in prevalence between study arms with 90% power and a 5% level of significance, estimated intracluster correlation coefficient (ICC) of 0.0033 and an anticipated attrition rate of 10%, a total of 20 clusters per arm with 105 women per cluster (ie, 2100 women per arm) will be required. The prevalence of anxiety is assumed to vary by ±5 percentage points between clusters. The coefficient of variation (CV) was estimated based on this range, and the ICC was then derived using the CV formula.^21 22^

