**Figure 2 F2:**
[figure not shown]
Study design and outcomes. BHU, Basic Health Unit; LHS, Lady Health Supervisors; LHWs, Lady Health Workers; WRA, Women of Reproductive Age.

The secondary outcome includes:

Effectiveness of intervention on mental health—defined by the prevalence of anxiety and depression among WRA in the intervention arm when compared with the control arm.

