### Data analysis

#### Quantitative component

The data collected and stored on the server will be exported to Stata version 18 for analysis. Data will be cleaned, and errors will be rectified under the guidance of the study investigators. Descriptive statistics will be presented: mean and SD, or median with IQRs for continuous variables, depending on the data distribution, and frequency distributions for categorical variables. Feasibility, acceptability and appropriateness of the intervention were assessed through proportions with 95% CIs. For mental health outcomes, difference-in-difference (DID) analyses will be conducted through logistic regression analysis, assuming parallel trends i.e., intervention and control arms had parallel trends in the outcomes before the intervention was introduced. The model incorporates an interaction term for time and intervention effect. The coefficient of the interaction term serves as DID estimate. Further, to address potential confounding, the DID will be adjusted for imbalanced factors at baseline. In addition, the model will also include covariates that are known to affect the outcome such as age, education, marital status, parity, socioeconomic status and trauma. For missing data on variables, the plan will be not to impute but treat this as missing and perform complete case analysis. All analysis will be adjusted to account for the cluster randomised design.

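### The stated 90% power is for comparing two prevalences at one time, not for the planned difference-in-difference interaction, whose power depends on correlations that the protocol does not give

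*Protocol article*

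**What the plan says.** All locations are in the protocol article.

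- **Sample Size, starting prevalence:** "The sample size was calculated based on an estimated anxiety prevalence of 25.6"%.
- **Sample Size, target:** "To detect a 20% relative difference in prevalence between study arms with 90% power and a 5% level of significance".
- **Sample Size, other inputs:** "estimated intracluster correlation coefficient (ICC) of 0.0033 and an anticipated attrition rate of 10"%. The ICC is derived from a between-cluster spread: "The prevalence of anxiety is assumed to vary by ±5 percentage points between clusters".
- **Sample Size, result:** "a total of 20 clusters per arm with 105 women per cluster (ie, 2100 women per arm) will be required".
- **Outcomes:** the secondary outcome is effectiveness, "defined by the prevalence of anxiety and depression among WRA in the intervention arm when compared with the control arm".
- **Quantitative component:** for the mental health outcomes, "difference-in-difference (DID) analyses will be conducted through logistic regression analysis, assuming parallel trends". The model has a time-by-intervention term, and "The coefficient of the interaction term serves as DID estimate".

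The Sample Size section mentions no baseline wave, no change over time, no baseline-endline correlation and no odds ratio.

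**The concern.** A power statement belongs to one particular test. The inputs here are one prevalence, one relative difference, a cross-sectional ICC and an attrition rate, which are the ingredients of an endline-only comparison of two arms. The planned test uses four arm-by-time cells. It subtracts a baseline contrast that carries its own sampling error, and gains some of that back to the extent that baseline and endline results are correlated within women and within clusters. Its power can therefore lie below or above that of the endline comparison.

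At stake is how the effectiveness result is read. Effectiveness is the only outcome that the sample size addresses. A null interaction would be taken as fairly strong evidence against a 20% relative reduction if readers trusted the 90%, and that trust is not yet earned for this test.

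**Working it through.** **1. Reproduce the stated sample size.** Inputs from the Sample Size section: p0 = 0.256; p1 = 0.8 × 0.256 = 0.2048 (difference read as a reduction); power 90%; 5% read as two-sided; ICC 0.0033; attrition 10%; 105 women per cluster.

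- The usual two-proportion formula gives 1420 women per arm.
- Design effect = 1 + (105 − 1) × 0.0033 = 1.343.
- 1420 × 1.343 = 1907, and 1907 / 0.90 = 2119 per arm, within 1% of 2100. With the retained cluster size of 94.5 the result is about 2065.
- The ICC is also purely cross-sectional. Reading ±5 points as ±2 SD gives SD 0.025, and 0.025² / (0.256 × 0.744) = 0.0033.

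Power of that endline comparison with 20 × 94.5 = 1890 analysed women per arm:

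- Design effect = 1 + 93.5 × 0.0033 = 1.309.
- SE = √[(0.1905 + 0.1629) × 1.309 / 1890] = 0.01564.
- z = 0.0512 / 0.01564 = 3.27, and power = Φ(3.27 − 1.96) = 90.5%.

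So the stated 90% belongs to this test.

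**2. Power of the planned interaction, same sample.** Assumptions: 25.6% in three cells and 20.48% in the intervention arm at endline. The interaction odds ratio is (0.2048/0.7952) / (0.256/0.744) = 0.748, log −0.290. Within-woman correlation r and cluster autocorrelation c are assumptions, because the protocol gives neither.

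Let a = 1/(0.256 × 0.744) = 5.250 and b = 1/(0.2048 × 0.7952) = 6.140. Then

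Var = [(3a + b) × D − 2(a + √(ab)) × F] / 1890,

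with D = 1.309 and F = (1 − ICC) r + 94.5 × ICC × c = 0.9967 r + 0.3119 c.

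Numerically, Var = [28.65 − 21.86 F] / 1890, and power = Φ(0.290/√Var − 1.96).

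- r = 0, c = 0: Var = 0.01516, SE = 0.123, z = 2.35, power 65%.
- r = 0.4, c = 0.8: F = 0.648, Var = 0.00766, SE = 0.0875, z = 3.31, power 91%.

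| r (within woman) | c (cluster) | Power |
|---|---|---|
| 0 | 0 | 65% |
| 0 | 0.8 | 74% |
| 0.2 | 0.8 | 83% |
| 0.3 | 0.8 | 87% |
| 0.4 | 0.8 | 91% |
| 0.5 | 0.8 | 95% |
| 0.3 | 0.5 | 83% |
| 0.4 | 0.5 | 87% |
| 0.5 | 0.5 | 91% |
| 0 | 1 | 77% |

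**3. Where 90% is reached.** Solving the same formula, r must be about 0.37 when c = 0.8 and about 0.47 when c = 0.5. At the extremes it is about 0.31 (c = 1) and 0.62 (c = 0). With different women at the two surveys (r = 0), power does not exceed 77% even when c = 1.

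**4. Does the protocol settle r?** The attrition allowance, and the statement under Baseline and endline data collection that participants are assessed at both times, point towards a cohort. Table 2, however, describes the endline as covering all women of reproductive age in the study Union Councils. No sentence says plainly that the baseline women are re-interviewed, and no correlation is given.

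**The case against.** The strongest reply is that the direction of the error is unknown. The attrition allowance only makes sense if women are followed, and in a cohort with within-woman correlation of 0.4 or more (at c = 0.8) the planned interaction meets or exceeds 90%. This stands. A reader might infer that the trial is underpowered, but the documents do not support that. They show only that the stated figure was calculated for another test.

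A second reply concerns scale. Because the interaction is a ratio of odds ratios, a reader might infer that it can show an effect where there is none. For example, if prevalence fell 6 points in both arms, from 35% in control and from 20% in intervention, the interaction odds ratio would be 0.858. That inference fails here. The protocol states its effect as a relative difference and nowhere defines it in percentage points. On the relative scale these arms do differ: (0.14/0.20) / (0.29/0.35) = 0.845, close to 0.858. The example baselines also lie outside the ±5-point range around 25.6% that the protocol assumes for its clusters. At a given starting prevalence the 20% relative difference converts directly to an odds ratio. The choice of scale is therefore a preference and not an error.

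Third, effectiveness is the secondary objective, and the primary outcomes are feasibility proportions reported with confidence intervals. This stands and limits the severity. It does not remove the point, because the mismatch lies between two passages of the same document and does not turn on detail that a separate analysis plan might supply.

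**Conclusion.** The point holds as a mismatch between the powered contrast and the planned test. The 90% is the power of a single-survey comparison (90.5% on recalculation). For the interaction, the same sample gives about 65% with no correlation over time and, at a cluster autocorrelation of 0.8, about 74% to 95% as the within-woman correlation goes from 0 to 0.5. The claim of 90% needs re-interviewed women and a within-woman correlation of roughly 0.4 to 0.5 or more for cluster autocorrelations of 0.8 to 0.5.

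These figures grant the planned 20 clusters per arm, take 25.6% in three cells, use 94.5 women per cluster at both surveys, and ignore covariate adjustment. With all 105 women analysed at both surveys, the no-correlation figure is 69%. The defect affects the power statement. It does not bias the effect estimate. It should be fixed, at moderate severity, because it concerns a secondary outcome.

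**What to change.** Rewrite the power statement in the Sample Size section for the interaction contrast. Give:

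- the target odds ratio (0.748 for 25.6% against 20.48%) and the assumed prevalence in each arm-by-time cell;
- whether the same women are surveyed at baseline and endline;
- the assumed within-woman correlation and cluster autocorrelation, with power over a range such as the table above.

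The cost is one rewritten paragraph, with no new data and no change to the model. The drawback is that the stated power may become less favourable. Reporting the effect in percentage points by marginal standardisation, or running the same analysis on continuous GAD-7 and PHQ-9 scores, would be optional supporting work. Neither is needed to resolve this point.

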#### Hiring and training

The team for screening and delivering the intervention will include LHWs, LHS and BHU facility staff. The project will provide training to 20 LHWs in the intervention study arm to conduct household visits and administer screening tools. 12 female Senior Research Assistants (SRAs) along with four male SRAs will be recruited to assist.

The selected LHWs and LHS in the intervention clusters will receive training by the research team on screening using GAD-2 and PHQ-2, referral and provision of mental health awareness and resilience-building sessions. All BHU facility doctors will acquire training on assessment using GAD-7 and PHQ-9 of incoming referrals classified as screen-positive cases by LHWs, selection and administration of the most appropriate treatment strategies for mild or moderate cases (including counselling or psychoeducation for mild and moderate cases), and management and process of referral of severe cases for specialised care. Pre-training and post-training assessment of knowledge will be conducted for LHWs and LHS and communication and counselling skills for BHU or rural health clinic (RHC) facility staff.

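### The 90% power is calculated for 20 clusters per arm, but only 4 Union Councils per arm are assigned, so the assigned design does not support it

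*Protocol article*

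**What the plan says.** **Sample Size.** The target is "To detect a 20% relative difference in prevalence between study arms with 90% power and a 5% level of significance", from an anxiety prevalence of 25.6%, with an "estimated intracluster correlation coefficient (ICC) of 0.0033" and 10% attrition. The result is that "a total of 20 clusters per arm with 105 women per cluster (ie, 2100 women per arm) will be required". The ICC is derived from an assumed variation of ±5 percentage points between clusters. The section does not say what a cluster is.

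**Study site.** Here "8 flood-affected Union Councils (UCs) were purposely chosen as they were the most severely affected and assigned into two groups": 4 UCs on one side of the Taluka Headquarters for the intervention and 4 on the other side for control. Each UC has one Basic Health Unit (BHU). The descriptions of the two arms repeat four UCs each.

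**Hiring and training.** "The project will provide training to 20 LHWs in the intervention study arm". This is the only other count of 20 that could explain the clusters.

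**Data analysis, Quantitative component.** Mental health outcomes are compared by difference-in-difference logistic regression, adjusted for what is called a cluster randomised design. The level of clustering is not named.

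**Objectives and Outcomes.** Effectiveness is the secondary objective. The primary outcomes are feasibility, acceptability and appropriateness.

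**The concern.** The unit in the power calculation is not the unit placed into arms. Every woman in a UC is in the same arm, and screen-positive women in the intervention UCs go to the BHU of their own UC. Any UC-level difference in flood exposure, services or staff therefore falls wholly in one arm. If the 20 clusters are Lady Health Worker (LHW) areas, they are nested in 4 UCs and were not assigned separately.

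Two things follow. The between-arm comparison has 8 assigned units rather than 40, which costs degrees of freedom whatever the ICC. Any correlation between women in the same UC but in different LHW areas also adds variance that the calculation leaves out.

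At stake is the stated chance of detecting the planned effect. If it is well below 90%, the protocol overstates what an inconclusive effectiveness result would tell its reader.

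**Working it through.** **Inputs from Sample Size.** p1 = 0.256. A 20% relative reduction gives p2 = 0.2048 and d = 0.0512. The direction (a reduction) and a two-sided 5% test are assumed; a one-sided test gives about 1,727 women per arm and does not reproduce the stated size. ICC = 0.0033. Women per arm: 2,100 enrolled, 2,100 × 0.9 = 1,890 analysed. Sum of binomial variances: 0.256 × 0.744 + 0.2048 × 0.7952 = 0.1905 + 0.1629 = 0.3533.

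**Step 1: reproduce the plan.**
- ICC: reading ±5 points as 2 SD gives SD 0.025, CV = 0.025/0.256 = 0.0977, and ICC = 0.025² / (0.256 × 0.744) = 0.0033.
- Without clustering: n = (1.960 + 1.282)² × 0.3533 / 0.0512² = 1,416 per arm (1,420 with the pooled-variance formula).
- Design effect at 105 women per cluster: 1 + 104 × 0.0033 = 1.343. Then 1,420 × 1.343 / 0.9 = 2,119, against the stated 2,100.
- The Hayes–Bennett formula with 94.5 analysed women per cluster gives 20.1 clusters per arm.
- Power with 20 clusters of 94.5: design effect 1 + 93.5 × 0.0033 = 1.309, effective n = 1,890 / 1.309 = 1,444, power 90.5% (normal reference).

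The arithmetic is right for 20 independently assigned clusters per arm.

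**Step 2: same comparison, 4 UCs per arm.** Analysed women per UC: 1,890 / 4 = 472.5. Degrees of freedom: 2 × (4 − 1) = 6. Noncentrality = d / √(0.3533 / effective n), referred to a noncentral t with 6 df (critical value 2.447).

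| Clustering | Design effect | Effective n per arm | Noncentrality | Power, t on 6 df |
|---|---|---|---|---|
| None at any level | 1.00 | 1,890 | 3.74 | 87% |
| 0.0033 below UC level only | 1 + 93.5 × 0.0033 = 1.309 | 1,444 | 3.27 | 78% |
| UC-level ICC 0.001 (assumption) | 1 + 471.5 × 0.001 = 1.472 | 1,284 | 3.09 | 73% |
| UC-level ICC 0.0033 (assumption) | 1 + 471.5 × 0.0033 = 2.556 | 739 | 2.34 | 50% |
| UC-level ICC 0.01 (assumption) | 1 + 471.5 × 0.01 = 5.715 | 331 | 1.57 | 26% |

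The UC-level rows use a single ICC for the whole UC. If 0.001 is instead the correlation between LHW areas of one UC, with 0.0033 within an LHW area, the design effect is 1 + 93.5 × 0.0033 + 378 × 0.001 = 1.687 and power is 67%. With a normal reference, the UC-level 0.0033 case gives 65%. A simulated t-test on 4 versus 4 cluster proportions gives 50% for that case on 6 df.

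**Step 3: detectable difference at 90% power, 6 df.** With 0.0033 below UC level only: 25.6% against 19.5%, 6.1 points, 24% relative. With 0.0033 at UC level: 25.6% against 17.3%, 8.3 points, 32% relative.

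**Step 4: could more women restore 90%?** Not if 0.0033 holds at UC level. Even under the normal formula the number of clusters per arm must exceed 1,420 × 0.0033 = 4.7, and there are 4.

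**The case against.** The strongest reply is that the low figures are not the plan's own. The ICC of 0.0033 was derived for clusters of 105 women, and no section gives a UC-level value. Correlation across a whole UC may be weaker than within one LHW area. This stands. A reader might infer that the plan's own inputs imply 50% power and a 32% detectable reduction. They do so only if 0.0033 is carried up to UC level, which is an assumption.

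Second, the rework is not the power of the planned analysis. The difference-in-difference model uses a baseline survey in both arms and covariates. It can remove stable differences between UCs, and it can also add variance. The document gives no inputs to settle which dominates. It would go too far to say that the study will have between 50% and 78% power; the figures are a like-for-like correction of the Sample Size calculation. The 6 df likewise belong to a comparison of assigned units. Data analysis does not name the level, and an analysis plan not shown may do so.

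Third, the link between the 20 clusters and the 20 LHWs is an inference. The document does not equate them, and it gives no LHW count for the control arm.

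Fourth, effectiveness is secondary, and the feasibility proportions with their confidence intervals do not depend on this power claim. Nothing in the document says that a null result would be presented as proof of no effect.

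None of this reconciles 20 clusters with 4 UCs. Keeping about 90% requires both no correlation at UC level and an analysis that treats the smaller clusters as independent. The document states neither. On 6 df, even no clustering at any level gives 87%.

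**Conclusion.** The point holds as a mismatch between the unit in the power calculation and the unit assigned; the stated arithmetic itself is correct. In a like-for-like rework with 4 UCs per arm, 1,890 analysed women per arm and 6 df, power for a 20% relative reduction is about 78% at best with the plan's ICC. It is lower to the extent that women in the same UC are correlated across LHW areas. The lower values (73%, 50%, 26%) each rest on an assumed UC-level ICC, and all the figures concern an endline two-proportion comparison rather than the difference-in-difference model. The claim of 90% power for a 20% relative difference is not supported by the assigned design. This bears on the secondary effectiveness comparison, although the whole sample size is built on it.

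**What to change.** Revise the Sample Size section to:

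- define the cluster, and if it is the LHW area, say so and give the number in each arm;
- reconcile it with Study site by naming the UC as the assigned unit, 4 per arm with about 2,100 / 4 = 525 women each, and any smaller cluster as a level below it;
- restate power and the detectable difference for 4 UCs per arm over a range of UC-level ICCs labelled as assumptions, with the degrees of freedom used;
- withdraw the claim of 90% power for a 20% relative difference in the effectiveness comparison;
- note that the difference-in-difference model may shift these figures, and give its inputs (for example the correlation between baseline and endline) if they are available.

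The cost is one rewritten paragraph. No extra women or fieldwork are needed. The only downside is a less favourable stated power.
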